## Abstract

**Background:**

The prevalence of mental disorders worldwide is very high. The guideline-oriented care of patients depends on early diagnosis and regular and valid evaluation of their treatment to be able to quickly intervene should the patient’s mental health deteriorate. To ensure effective treatment, the level of experience of the physician or therapist is of importance, both in the initial diagnosis and in the treatment of mental illnesses. Nevertheless, experienced physicians and psychotherapists are not available in enough numbers everywhere, especially in rural areas or in less developed countries. Human speech can reveal a speaker’s mental state by altering its noncontent aspects (speech melody, intonations, speech rate, etc). This is noticeable in both the clinic and everyday life by having prior knowledge of the normal speech patterns of the affected person, and with enough time spent listening to the patient. However, this time and experience are often unavailable, leaving unused opportunities to capture linguistic, noncontent information. To improve the care of patients with mental disorders, we have developed a concept for assessing their most important mental parameters through a noncontent analysis of their active speech. Using speech analysis for the assessment and tracking of mental health patients opens up the possibility of remote, automatic, and ongoing evaluation when used with patients’ smartphones, as part of the current trends toward the increasing use of digital and mobile health tools.

**Objective:**

The primary objective of this study is to evaluate measurements of participants' mental state by comparing the analysis of noncontent speech parameters to the results of several psychological questionnaires (Symptom Checklist-90 [SCL-90], the Patient Health Questionnaire [PHQ], and the Big 5 Test).

**Methods:**

In this paper, we described a case-controlled study (with a case group and one control group). The participants will be recruited in an outpatient neuropsychiatric treatment center. Inclusion criteria are a neurological or psychiatric diagnosis made by a specialist, no terminal or life-threatening illnesses, and fluent use of the German language. Exclusion criteria include psychosis, dementia, speech or language disorders in neurological diseases, addiction history, a suicide attempt recently or in the last 12 months, or insufficient language skills. The measuring instrument will be the VoiceSense digital voice analysis tool, which enables the analysis of 200 specific speech parameters, and the assessment of findings using psychometric instruments and questionnaires (SCL-90, PHQ, Big 5 Test).

**Results:**

The study is ongoing as of September 2019, but we have enrolled 254 participants. There have been 161 measurements completed at timepoint 1, and a total of 62 participants have completed every psychological and speech analysis measurement.

**Conclusions:**

It appears that the tone and modulation of speech are as important, if not more so, than the content, and should not be underestimated. This is particularly evident in the interpretation of the psychological findings thus far acquired. Therefore, the application of a software analysis tool could increase the accuracy of finding assessments and improve patient care.

**Trial Registration:**

ClinicalTrials.gov NCT03700008; https://clinicaltrials.gov/ct2/show/NCT03700008

**International Registered Report Identifier (IRRID):**

PRR1-10.2196/13852

## Introduction

### Human Language

Human language is a fundamental ability which, in addition to social interaction, primarily serves the exchange of feelings; however, in the sense of an inner dialogue, it also serves as a means of self-perception and self-reflection [1]. This establishes a relationship between pure content as an expression of cognitive performance and emotional content in the sense of affective meaning. This close connection between emotion and cognition, especially with language and speech, has been scientifically researched within the framework of relational frame theory for many years [2]. Human language as a form of expression, with human listening on the other side, has been the basis of professional therapeutic support for mental disorders for more than 100 years [3,4]. The recent treatment developments regarding linguistic and psychological research in relational frame theory have been acceptance-based treatments, such as acceptance and commitment therapy [5]. 

Due to the increasing global frequency of mental disorders, their safe detection and treatment is very important. According to World Health Organization calculations [6], depression alone will be the second greatest burden of disease in the world in 2020. Other mental disorders, such as neurodevelopmental disorders (attention deficit hyperactivity disorder [ADHD], autism spectrum disorders, etc [7,8]) or personality disorders [9], which have been increasing in recent years, also cause significant individual stress and have a societal impact due to the loss of potential productivity and treatment costs [10]. Early detection and treatment of mental disorders is, therefore, a major factor in preventing these problems, as is the avoidance of deterioration. However, there is currently no objective, ideal physiological parameter available for this task.

Since the 1990s, attempts have been made to determine the emotional state of a speaker by analyzing the content of their speech and the linguistic structure [11]. There have been positive results thus far, with high specificity and sensitivity in some subjects when using suitable parameters, like in cases where depressive disorders have been detected [12-14]. As a result, there has been intensive development in the automation of such analyses, with continuing positive results [14]. However, so far dissemination of such analyses, such as in the early detection, diagnosis, or assessment of mental disorders, has not occurred in broad clinical practice but has been described in a few single cases [15,16]. The reasons for this may be complex, but it may be due to the high technical effort required to perform these analyses that have led to them not being well reflected in outpatient care practice [17]. Also, resentment against machine diagnosis or very technical measurements may have played a role that should not be underestimated. Finally, the diagnostic and prognostic validity of such measures still needs to be proven.

In the last decade, electronic assistants have taken up considerable space in all areas of life, first through computerization and later via smartphones [18]. In medicine, and especially in psychiatry and psychotherapy, numerous programs, online tools, and coaching applications are now available and have seen increasing acceptance [19]. At the same time, the technical effort that needs to be expended to create a high-quality, medically or psychologically useful application for use in the clinic has decreased [20,21]. The applications that can be implemented in this way are even more complex and extensive than previously thought possible. It may, therefore, make sense to use these new technical possibilities and examine whether the analysis of language, especially the noncontent aspects (eg, speech flow, speech melody, expression), can be used by a differentiated algorithm to assess the mental state of a subject. It is possible that they could also measure the course of mental illness, the quality of life of patients with chronic mental illnesses, and patients' well-being [22].

The study presented here uses a noncontent linguistic analysis algorithm developed by VoiceSense, a company specializing in prosodic speech analysis, which links speech patterns to behavioral tendencies. The analysis is commercially used for personal risk assessment by banks and insurance companies, for candidate assessment by human resources companies, and customer analytics by enterprise call centers. The current study would provide a structured setting for the differentiated evaluation of psychopathological factors (effects, personality aspects, psychomotor factors, etc) by this speech pattern analysis.

### Research Objectives

The primary objective of this study is to evaluate the measurements of the mental state of the participants by comparing the analysis of noncontent speech parameters to the results of several psychological questionnaires (Symptom Checklist-90 [SCL-90], the Patient Health Questionnaire [PHQ], and the Big 5 Test). We hypothesized that the emotional state of mind, the behavioral patterns, the well-being, and some of the personality traits of the participants could be identified using the prosodic analysis algorithm. A second hypothesis is that the diagnosis could be confirmed by the application of the analysis program, and a distinction can be made between different psychopathologically-defined syndromes.

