### Linguistic Algorithm and Recording System

#### Audio Collection

Speech utterances of the subjects will be sampled using the VoiceSense mobile app, which will be installed on the tablets (BENEVE Co, 10.1-inch screen, 32 gigabytes of memory, Android version 7.0) of the research examiners. The recordings will be taken over 1-3 separate sessions throughout the study: the initial interview, the first follow-up session after 2-4 weeks, and the second follow-up session after another 2-4 week period. In each of those sessions, the research examiners will activate the app by logging into it with a dedicated username and password that was prepared in advance for each subject (the username and password do not reveal the subject’s identification). The app then presents 9 general questions (eg, “Please describe in a few sentences how was your day yesterday”). The subject presses record and answers, and when finished they will press stop and the app will present a second question for the subject to answer. The app will count the recorded time to verify that at least 120 seconds are recorded, but if after nine answers there is still not enough recording time then the app will present an increasing number of questions till the time requirement is met. Once enough speech is recorded, the app will send the recorded audio to the VoiceSense cloud server for analysis. The content of the subject’s answers is not important for the analysis; therefore, the questions are designed in a general manner to enable collection of the natural speech patterns of the subjects. The recordings will be done in a quiet room in the Neuropsychiatric Center Hamburg, which is reserved for diagnostic purposes. The examiner will leave the room while the recording is done, to make the subjects feel more comfortable and to not influence their free speech.

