### Study Design and Data Protection

This study is a case-controlled study with a case group and a control group to identify the best target population for measuring speech patterns with the VoiceSense app. We adhered to the Consolidated Standards of Reporting Trials (CONSORT) guidelines in the design of the trial.

In the first step, the participants will be grouped by the physician or psychotherapist into a control group (participants without mental disorders) or a case group (participants with mental disorders). All participants will provide written informed consent after being given detailed information by the treating therapist or physician. The original forms will be stored in a closed cabinet, but the participants will receive a copy. Second, they will receive a pseudonymized label for the blinded inhouse-rater to work with the questionnaires, and for the data center for the speech-analysis. Neither the rater nor the data center will know the name and diagnosis of the participant. Data security and availability will be ensured every time, according to the European Union (EU) rules [29]. The participants’ data will be stored in a MySQL-Database. Within the project database, identifying data will be stored separately from the collected data, with only project staff with specifically conferred access rights able to access the identifying data. It is envisioned that the distribution of participants will correspond to the clinical distribution in the Neuropsychiatric Center with different degrees of severity of mental disorders (about 25% mild, about 50% moderate, about 25% severe). This should be checked by the study nurse every 2 weeks.

For documentation purposes, the presence or absence (in the case of neurological outpatients) of any psychiatric diagnosis will be screened using the PHQ-D [30]. Personality traits will then be measured with the Big 5 Test [23]. In the case of ADHD, we added a Visual Analogue Scale (ADHD-VAS) to identify the three main affective states (impulsivity, inattention, and hyperactivity). This will be done at baseline only.

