At baseline, at follow-up one (2-4 weeks after baseline), and follow-up two (2-4 weeks after follow-up 1), participants will be measured for mental distress using the SCL-90 [31]. They will then be asked to freely answer nine standardized questions, with a few sentences per question. These answers will be recorded for evaluation. If less than 120 seconds of free speech is possible, three more standardized questions will be asked and the answers to these will also be recorded. The recorded sentences will then be sent to the server to carry out the prosodic analysis. The results of the questionnaires and the results of the prosodic analysis will be stored in the patients’ records on file. Figure 1 shows the flow chart of the study.

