### Statistical Methods

It should be possible for the study team to evaluate the efficacy and effectiveness of the raw data from the linguistic analysis in correlation with the clinical data collected with the questionnaires. All statistical tests will be two-tailed and will be considered statistically significant at *P*<.05. A sample size of 166 subjects was calculated (effect size medium=0.30; alpha=0.05; 1–beta=0.95), and considering a drop-out rate of 15%, a total sample size of 190 patients was determined. 

Statistical analysis will be performed with R version 3.5.3 (The R Project, Vienna, Austria), and epidemiological data will be evaluated. Continuous variables will be described with the mean, standard deviation, median, minimum, maximum, and the 25th and 75th percentiles. Categorical variables will be described with percentages and absolute frequencies. The differences in continuous variables between the two groups will be evaluated with the Kruskal-Wallis test, followed by the Dunn multiple comparison test. The differences between the two diagnostic groups (psychiatric versus neurological diagnosis) for normally distributed data will be evaluated with a one-way analysis of variance (ANOVA), followed by the Newman-Keuls multiple comparison test. The normality of the distribution will be evaluated with the Kolmogorov-Smirnov test. Any correlation between the variables under evaluation will be assessed by the Spearman r correlation. To compare qualitative data, we will use the Chi-square test with the Yates correction or the Fisher exact test. Lastly, the variables will be grouped to their diagnostic groups according to the 10th edition of the International Statistical Classification of Diseases and Related Health Problems or the fifth edition of the Diagnostic and Statistical Manual of Mental Disorders, and a confirmative factor analysis will be done comparing these groups with the prosodic parameters.

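### The planned Big 5–speech correlation is unadjusted for distress, so the stated analysis, though not the data collected, cannot separate a trait signal from current state

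*Protocol article*

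**What the plan says.** The Protocol article's Research Objectives put two kinds of target in one hypothesis. Speech is to identify current state (emotional state, well-being), and also "some of the personality traits of the participants could be identified using the prosodic analysis algorithm".

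The measurements are set out under Study Design and Data Protection:

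- Trait: "Personality traits will then be measured with the Big 5 Test". The paragraph closes with "This will be done at baseline only", and the Big 5 Test is not among the follow-up measures, so a single baseline administration is the natural reading.
- State: at baseline and at both follow-ups, "participants will be measured for mental distress using the SCL-90".
- Speech: Audio Collection states that "The recordings will be taken over 1-3 separate sessions throughout the study", the first of them at the initial interview.
- Sample: participants are assigned to a "control group (participants without mental disorders) or a case group (participants with mental disorders"). The expected severity mix of the mental disorders is "about 25% mild, about 50% moderate, about 25% severe".

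Statistical Methods gives one rule for associations: "Any correlation between the variables under evaluation will be assessed by the Spearman r correlation". The other methods named there are group comparisons, tests for categorical data and a factor analysis that sets diagnostic groups against prosodic parameters. None of them sets trait against state.

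**The concern.** Self-rated personality scales can overlap with how distressed the respondent is on the day. Neuroticism is the obvious case. The article itself takes the other link for granted: its Abstract says that noncontent speech reveals mental state, and its Discussion treats this as established, at least for depression. With both links in place, a Big 5–speech correlation is expected even if speech says nothing about personality beyond current distress. Pooling patients with mental disorders and controls without them can widen the spread of distress and so strengthen this path.

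The two claims serve different purposes. The Abstract envisages ongoing tracking of patients, which needs a state measure. The Introduction mentions commercial use in candidate and personal risk assessment, where a stable characteristic is what matters. If a state effect is reported as trait identification, the second use appears supported when it is not.

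**Working it through.** **The plan's own figure.** Statistical Methods gives 166 subjects for effect size 0.30, two-sided alpha 0.05 and power 0.95. For a correlation, Fisher's z gives n = ((1.960 + 1.645)/atanh(0.30))² + 3 = (3.605/0.3095)² + 3 ≈ 139, so 166 is not reproduced this way. That is a separate matter. Below, 166 is used simply as the planned number.

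**Inputs.**

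- n = 166 and two-sided P<.05: Statistical Methods.
- Speech–distress correlation 0.30: an assumption. The plan's effect size is borrowed; the plan does not say that it refers to this pair.
- Big 5–distress correlation 0.3 to 0.7: an assumption; the documents give no value.
- Speech has no association with the trait other than through distress.

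**Step 1: induced correlation.** Under these inputs, r(trait, speech) = r(trait, distress) × r(distress, speech).

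**Step 2: chance of significance, by hand.** For normal data the Spearman value is (6/π)·arcsin(r/2). The chance of significance is about Φ(atanh(Spearman value)·√163 − 1.960), with √163 = 12.767. For r = 0.15, the Spearman value is 0.143, and 0.1444 × 12.767 = 1.843. Then 1.843 − 1.960 = −0.117, and Φ(−0.117) ≈ 0.45.

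**Step 3: simulation.** 4,000 runs per row, n=166, each for a single correlation:

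| Trait–distress r (assumed) | Induced r | Unadjusted Spearman significant |
|---|---|---|
| 0.3 | 0.09 | 20% |
| 0.5 | 0.15 | 45% |
| 0.6 | 0.18 | 61% |
| 0.7 | 0.21 | 73% |

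The hand calculation agrees with the simulated 45% in the second row. If speech is tied to distress more strongly, at 0.5, the rates at trait–distress 0.3, 0.5 and 0.7 are about 44–46%, 87–88% and 99%.

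**Step 4: what adjustment does.** The numerator of the partial correlation given distress is r(trait, speech) − r(trait, distress)·r(distress, speech). For the second row this is 0.15 − 0.5 × 0.30 = 0. In simulation the partial Spearman test is then significant in about 5% of studies if distress is measured without error. With an assumed reliability of 0.85 for the distress score:

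| Trait–distress r | Speech–distress 0.3 | Speech–distress 0.5 |
|---|---|---|
| 0.3 | 6% | 7% |
| 0.5 | 6% | 9% |
| 0.7 | 9% | 20% |

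Adjustment therefore removes most of the problem but not all of it.

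**Step 5: cost in sample size.** One covariate changes the Fisher formula from +3 to +4, so 140 are needed instead of 139 to detect a correlation of 0.30.

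**The case against.** Five points can be made for the plan.

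- **The data are there.** A reader might infer that the study cannot separate trait from state at all. The documents do not support that: SCL-90, Big 5 and speech are all taken at baseline, and SCL-90 and speech are repeated. The gap lies in the stated analysis. This stands, with one limit: a single Big 5 administration leaves no way to check by repetition how far the Big 5 score itself moves with state.
- **The sample is not uniformly distressed.** A reader might take the severity mix to mean that three quarters of all participants are moderately or severely ill. It describes degrees of mental disorder, which does not fit controls without one, and no minimum distress is required for entry. This stands too, although a mixed sample does not remove the confounding.
- **An article condenses, and a fuller plan may adjust.** This is possible, and it is a reason for restraint. However, the article states a trait hypothesis and names a test for any correlation, and that test does not answer that hypothesis.
- **The hypothesis may mean only agreement with the Big 5 score.** On that reading the unadjusted correlation is relevant and should stay. It still does not show that traits, as distinct from state, are identified.
- **Adjustment can go too far.** If a trait is partly a disposition to distress, as neuroticism may be, holding SCL-90 constant removes genuine trait variance. The calculation above cannot show that an induced correlation is spurious in that sense; it shows only that there is no trait information beyond distress. This stands, and it rules out a pass/fail rule that would relabel parameters as state-related.

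**Conclusion.** The point holds as a weakness of the stated analysis. As written, a speech parameter that follows distress alone would be read as trait support in roughly 20% to 73% of studies at n=166, against a nominal 5%. These percentages rest on an assumed speech–distress correlation of 0.30 and an assumed Big 5–distress correlation of 0.3 to 0.7, neither of which the documents give. They apply to one correlation at a time, and scales that overlap little with distress would be little affected. Even the mildest case considered is about four times the nominal rate. The change is worth making because it is almost free. The documents do not support calling this a design failure.

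**What to change.** For every Big 5–speech correlation, add to Statistical Methods that the partial Spearman correlation given baseline SCL-90 global severity will be reported beside the unadjusted one. Add two sentences on interpretation:

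1. A correlation present only without adjustment is not distinguishable from a distress effect and will not be claimed as independent evidence that speech identifies a trait.
2. Such a correlation will not be relabelled as state-related, because adjustment can remove genuine trait variance and error in the SCL-90 leaves some confounding behind.

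Within-person stability of speech parameters across visits may be shown descriptively but should not serve as a criterion. The Results section reports only 67 participants at time point two, and distress that persists over the 4 to 8 weeks of follow-up would also look stable.

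The cost is analysis wording and one extra column of results, with no new data and almost no loss of precision. The downside is that fewer parameters can be claimed as trait markers, and the adjusted estimate may be conservative. The wording should be settled before the final calculations, which the article expects to start by November 2019.
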